To screen their food intake and physical activity (SQUASH), participants will fill in a three-day food diary before each CID 1+3 and on week 6. Gastrointestinal Symptom Rating Scale (GSRS) questionnaire will be completed the day before the CID1+3 and on weeks 2, 6 and 9. Therefore, we can screen whether the participant might experience gastrointestinal discomforts during the intervention period such as bloating and the outcomes are also relevant for our faecal microbiota analysis.

After completion of the trial, all data will be gathered and analyzed. Participants will receive a financial compensation for their efforts, as well as reimbursements of their travel expenses.

The total amount of time participants spend at our facilities will be around 36 hours (Screening: 1h; CID 1+2: 7+9.5h; Interview week 2, 6, 9: 3 x 0.5h; CID 3+4: 7+9.5h).

As mentioned before, CID 3 will be planned 12 weeks after the start of the intervention. The dietary supplement/placebo and the protein-rich diet will have to be continued until CID 3, which means that in some cases the intervention period will be not exactly 12 weeks, but a few days longer or shorter, depending on the availability of the participant. Logically, the investigators aim for CID 3 to be planned exactly 12 weeks after the start of the intervention. The reason the intervention needs to be continued until the day before CID 3, is to ensure possible acute effects of the intervention on the experiments/outcomes are comparable between participants. It is hypothesized that the small differences in total length of the intervention will not substantially interfere with the outcome measures.

The researchers aim to adhere to the proposed schedule of the test days. However, if necessary, test day schedules might have to be altered due to logistical reasons.

[figure not shown]

Figure 1. Study design

Tables 1 and 2. Clinical investigation day 1 and 2

| Clinical investigation day 1 |                                              |
|------------------------------|----------------------------------------------|
| 08.00u                       | Measuring anthropometrics                    |
| 08.15u                       | Multisugar test → start 24h urine collection |
| 08.45u                       | fMRI                                         |
| 10.00u                       | Subcutaneous adipose tissue biopsy           |
| 10.45u                       | Questionnaires + CANTAB                      |

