## 5. TREATMENT OF SUBJECTS

### 5.1 Investigational product/treatment

All participants will receive a high-protein diet during the entire trial (12 consecutive weeks in total, starting the day directly after CID 2 until the day prior to CID3). This diet will consist of 25 energy percentage (E%) protein, 30E% fat and 45E% carbohydrates. Proteins will be 45-50% plant-based and 50-55% animal-based, to ensure a resemblance to the current western diet consisting of mainly animal-based proteins, while simultaneously acting on the currently shifting trend in society towards more plant-based diets.

Furthermore, according to randomization, one group will receive a potato-pectin fibre mixture and the remaining participants will receive a placebo.

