### 8.3.3 Blood samples

During the study period, multiple blood samples will be taken, most of which will be drawn right before or during the hyperinsulinemic-euglycemic clamp. During the screening, fasting glucose, HbA1c, and liver and kidney function will be determined to assess eligibility. Also, on CID 2, CID 4 and in week 6, blood samples will be taken to assess the following elements:

Glucose, insulin, HbA1c, haemoglobin, leucocytes, C-reactive protein (CRP), interleukin 1 (IL-1), IL-2, IL-6, IL-8, IL-12, interferon-gamma (IFN- $\gamma$ ), lipopolysaccharide binding protein (LBP), lipopolysaccharides (LPS), triacylglycerol (TAG), high-density lipoprotein (HDL), low-density lipoprotein (LDL), total cholesterol, glucagon-like peptide 1 (GLP-1), peptide YY (PYY), acetate, propionate, butyrate, valerate, isovalerate, isobutyrate, lactate, free fatty acids (FAA), branched-chain fatty acids (BCFA), leptin, aspartate amino transferase (ASAT), alanine amino transferase (ALAT), creatinine, ureum, zonulin, dopamine, FACS on immune cells.

Specific blood samples will be needed during the hyperinsulinemic-euglycemic clamp.

All samples consist of a maximum of 10ml blood per sample and will be analysed by the laboratories of the MUMC+. The total amount of blood needed is ~380ml (screening 20ml, CID 1+2 165ml (baseline 15ml, clamp 150), week 6 10ml each, CID 3+4 165ml (endpoint 15ml, clamp 150)).

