### 8.3.4 Faecal samples

Participants will hand in a faecal sample on CID 2+CID 4 and in week 2 and 6 to determine the amount of faecal saccharolytic and proteolytic fermentation substrates (e.g. SCFA, and BCFA and indoles, respectively), energy content and the composition of the microbiome, using 16S RNA sequencing. A sample container will be provided for every collection.

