**8.3.10 Two-step hyperinsulinemic-euglycemic clamp**

To assess whole-body and tissue-specific insulin sensitivity, we will be performing a two-step hyperinsulinemic-euglycemic clamp, which is the gold standard to determine insulin sensitivity. The clamp will be performed on CID 2 and 4 and will take place after a >12h overnight fasting period and a standardized meal the evening before. Before starting the procedure, an intravenous canula will be inserted in an antecubital vein to provide intravenous access for insulin and glucose suppletion. Another intravenous canula will be inserted on the dorsal side of the contralateral hand to ensure intravenous access for blood sampling.

At  $t = 0$  minutes, a fasting blood sample (10ml) will be drawn, followed by infusion of a primed 6,6-H2-glucose tracer at 0.04mg/kg/min, which will be used to calculate endogenous glucose production (EGP), glucose appearance (Ra) and glucose disposal. Therefore, blood samples (6ml) will be drawn at  $t=90$ , 105 and 120 min. At  $t = 120$ min, insulin will be infused at a low,

constant rate of 10 mU/m^2/min for 3 hours to allow determination of hepatic glucose production. After 3 hours ( $t = 300\text{min}$ ), insulin infusion will be increased to 40 mU/m^2/min to inhibit EGP for 2.5 hours, providing insight in muscle insulin sensitivity. During insulin suppletion, plasma glucose levels will be measured every 5 minutes (1ml), upon which glucose (20% glucose solution) will be infused at 10-30ml/h to ensure a constant plasma glucose level of 4.8-5.2 mmol/l during the clamp. Afterwards, the total amount of infused glucose can be used to determine insulin sensitivity. Additional blood samples (6ml) will be drawn at  $t = 180, 240, 270, 285, 400, 420, 435$  and 450 minutes.

At  $t = 450\text{min}$ , insulin infusion will be terminated and glucose infusion will be slowly reduced to zero to ensure a safe normalisation of glucose homeostasis. Additional dietary supplements will be provided (sandwiches, drinks) to prevent a hypoglycemic state.

During the clamp, an indirect calorimetry will be performed, which will be described below.

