### 8.3.11 Indirect calorimetry

During the hyperinsulinemic-euglycemic clamp, an indirect calorimetry will be performed using a ventilated hood (Omnical, Maastricht Instruments, Maastricht). Measurements will take place during the basal, low insulin and high insulin infusion for 30 minutes (i.e. starting at  $t = 90, t = 270$  and  $t = 420$  minutes). During calorimetry, a hood will be placed over the subject's head to enable a continuous breath analysis for calculation of energy expenditure, and fat and carbohydrate oxidation. Data can then be used to determine resting metabolic rate, energy expenditure and total rate of fat and carbohydrate oxidation using the equations of Weir and Frayn.(46, 47) Nitrogen (N) excretion will be calculated based on the assumption that protein oxidation represents 15% of total energy expenditure. Additionally, urinary nitrogen will be analyzed as described before.

Calculations:

$$\text{Energy Expenditure (EE) (kJ/min)} = (3.9 \cdot \text{VO}_2) + (1.1 \cdot \text{VCO}_2)$$

$$\text{Carbohydrate oxidation (CHO) (g/min)} = (4.55 \cdot \text{VCO}_2) - (3.21 \cdot \text{VO}_2) - (2.87 \cdot \text{N})$$

$$\text{Fat oxidation (FAT) (g/min)} = (1.67 \cdot \text{VO}_2) - (1.67 \cdot \text{VCO}_2) - (1.92 \cdot \text{N})$$

$$\text{N (g/min)} = ((0.15 \cdot \text{EE})/17)/6.25$$

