### 8.3.14 Dietary intervention

At the end of CID 2, participants receive the assigned intervention (potato-pectin fibre mixture or placebo), in a blinded manner to both the participant and original investigator. Participants will start using the dietary supplement the day after CID 2 and continue to do so for 84 consecutive days. The assigned supplement should be consumed thrice daily during breakfast, lunch and dinner. Along with the dietary supplement, all participants should consume a diet high in proteins (see below). This diet will be composed in collaboration with a dietician to provide a diet suitable to each individual's needs and taste. Furthermore, subjects are asked to consume  $\leq 1$  alcohol units/day, based on the national dietary guidelines.(53)

Additionally, all participants will follow a diet high in proteins alongside the dietary supplement, of which the exact composition will be discussed individually to establish a diet suited to the participants' needs and taste. The energy requirements for this diet will be estimated using indirect calorimetry. The diet will consist of 25 energy percentage (E%) protein mixture, 30E% fat and 45E% carbohydrate. Proteins will be 45-50% plant-based and 50-55% animal-based, to ensure a resemblance to the current western diet consisting of mainly animal-based proteins, while simultaneously acting on the currently shifting trend into more plant-based protein-rich components.

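### Supplement and diet stop the day before CID 3, but the primary clamp is at CID 4, so the primary endpoint is measured off treatment after an interval that the text does not fix

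*Protocol*

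**What the plan says.** **When intake stops.** Section 3 has the supplement or placebo and the diet run on: "The dietary supplement/placebo and the protein-rich diet will have to be continued until CID 3". It makes the day before CID 3 the last day, and its reason for this timing "is to ensure possible acute effects of the intervention on the experiments/outcomes are comparable between participants". Section 5.1 sets the same limits for the diet: "12 consecutive weeks in total, starting the day directly after CID 2 until the day prior to CID3". Section 8.3.14 says: "Participants will start using the dietary supplement the day after CID 2 and continue to do so for 84 consecutive days".

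**When the endpoint is measured.** Section 8.3.10: "The clamp will be performed on CID 2 and 4". Table 2 also puts the clamp on the second visit of the pair. Calorimetry is tied to it (Section 8.3.11): "During the hyperinsulinemic-euglycemic clamp, an indirect calorimetry will be performed". The endpoint blood samples are at the same visit (Section 8.3.3): "on CID 2, CID 4 and in week 6, blood samples will be taken".

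**Spacing of visits.** Section 3 puts CID 2 at least 2 days, and preferably no more than 2 weeks, after CID 1. It describes CID 3 and CID 4 as similar to CID 1 and CID 2 and places both after the 12 weeks of intervention. It gives 13 weeks for the whole trial period after screening and randomisation. The text states no interval between CID 3 and CID 4.

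**The concern.** Section 3 sets out to determine the 12-week impact of the fibre mixture on tissue-specific insulin sensitivity. If intake ends before CID 3, the clamp at CID 4 shows what remains of that impact some days later. The high-protein diet, against which the fibre is to be tested, has stopped too.

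The protocol itself recognises that recency of intake can matter: it fixes the stop relative to CID 3 so that acute effects are comparable between participants. That protects the tests assigned to CID 3 (for example DEXA, fMRI and cognitive testing), but not the measurement on which the trial is powered. If the interval to CID 4 varies, participants also reach the clamp after different numbers of days without the supplement.

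At stake are a smaller fibre-placebo difference, if the effect fades on stopping, and extra between-participant variance in the primary endpoint.

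**Working it through.** **1. Duration.** 12 weeks x 7 = 84 days, so Section 8.3.14 agrees with the nominal 12 weeks. Number the intake days 1 to 84. CID 3 is then day 85 and CID 4 is day 85 + k, where k is the CID 3 to CID 4 interval in days.

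**2. Days from last intake day to measurement.**

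- CID 3 tests: 85 - 84 = 1 day, in everyone.
- Clamp at CID 4: (85 + k) - 84 = k + 1 days.

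**3. What the text implies for k.**

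- Lower end. Assume the 2-day minimum between CID 1 and CID 2 also applies to CID 3 and CID 4. Then k is at least 2 and the clamp is at least 3 days after last intake.
- 13 weeks counted from CID 1 to CID 4, both included (assumption). With CID 1 on day 0 and CID 2 on day a, CID 4 is on day a + 85 + k. The count is a + k + 86 = 91, so a + k = 5. With a at least 2, k is at most 3, and the clamp is at most 4 days after last intake.
- 13 weeks counted from the first intake day (assumption). 85 + k = 91 gives k = 6, so the clamp is 7 days after last intake.

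Section 3 does not define where its 13 weeks start. The total therefore suggests a few days to about a week, but sets no firm limit.

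**4. Which measurements are affected.**

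| Measurement | Visit | Days since last intake day |
|---|---|---|
| DEXA, fMRI, cognitive tests | CID 3 | 1 |
| Clamp (primary), its calorimetry, endpoint blood samples | CID 4 | k + 1, not fixed |

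**5. Can a power loss be derived?** No; the document gives no rate at which the effect fades. For orientation only, Section 4.4 gives a difference of 2.86 and a residual SD of sqrt(1 - 0.73²) x 3.95 = 2.70, so d = 2.86/2.70 = 1.059. A two-sided t test at alpha 0.05 and 80% power needs 16 per arm, or 16/0.8 = 20 per arm with 20% dropout; the plan has 22. With 44 x 0.8 = 35 completers (17 + 18), power is 86.0% and falls to 80% if 7.8% of the effect is lost (difference 2.64). With 22 + 22, power is 92.9% and the tolerated loss is 18.4% (difference 2.33). These figures show the margin; they do not show that any of it is used.

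**6. Cost of continuing to the day before CID 4.** Extra intake days = k, doses = 3k, grams = 15k, total exposure = 84 + k days.

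- k = 2: 6 doses, 30 g, 86 days.
- k = 4: 12 doses, 60 g, 88 days.

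**The case against.** The strongest reply is that the timing is deliberate. Section 3 places both end visits after the 12 weeks, the visit order mirrors baseline, and a clamp a few days after 84 days of intake can still be read as a 12-week effect. It is true that these sections do not contradict one another. But no reason is given for measuring the primary outcome after stopping, and the only reason given for timing points the other way.

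Figure 1 is not shown and may give the visit spacing. That could settle the interval, but it would not cancel the written stop date.

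Continuing intake would also put the last dose on the evening before the clamp, with the standardised meal, so an acute effect of fibre or maltodextrin could enter the measurement. This is a real trade-off. It does not defeat the change, because the protocol already accepts that condition for the CID 3 tests.

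Several stronger readings are tempting and not supported:

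- *The clamp may be up to 15 days off treatment.* This applies the preferred 2-week limit for CID 1 to CID 2 to the end visits. CID 4 would then fall on day 85 + 14 = 99, beyond the 91 days of a 13-week period.
- *The faecal endpoints are off treatment too.* Section 8.3.4 says "Participants will hand in a faecal sample on CID 2+CID 4 and in week 2 and 6". It fixes the day of delivery; the day of collection is not stated.
- *The comparison is biased or underpowered.* Both arms stop alike, and the document offers no basis for a loss of effect of any particular size.

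**Conclusion.** The point holds as a correctable flaw in the timing of the primary measurement. The text stops supplement and diet the day before CID 3 and measures the primary endpoint at CID 4, without continuing intake or fixing the interval. The clamp comes at least 3 days after last intake (assuming the 2-day minimum carries over), and probably a few days to about a week (assuming the 13 weeks cover the period up to CID 4), against 1 day for the CID 3 tests. The stated aim of comparable acute effects is met for those tests and not for the clamp.

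Neither between-arm bias nor an inflated type I error follows. The consequence is possible dilution and added variance of unknown size. The case for acting rests on the low cost of the change and the importance of the endpoint, not on a demonstrated loss.

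**What to change.** - In Sections 3, 5.1 and 8.3.14, continue supplement or placebo and the high-protein diet until the day before CID 4, replacing the fixed 84 days. The clamp then follows the last intake day by 1 day in everyone.
- Set a short CID 3 to CID 4 window, for example 2 to 4 days (the width is for the sponsor to choose), and keep the visit order as at baseline.
- Keep the last dose at the same time relative to the standardised meal and the overnight fast in all participants.
- Record days since last intake at the clamp.

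**Cost.** Revised wording and participant instructions, and an amendment notified to the ethics committee (Section 12.3). With a 2 to 4 day window, each participant takes 6 to 12 more doses, and exposure at CID 4 is 86 to 88 days. Section 6.8 already allows extra sachets. No visit or procedure is added. The window should be set together with the extension, since a longer gap would lengthen exposure day for day.

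**Alternative.** If a measurement after withdrawal is what the sponsor wants, the protocol should say so and fix the same short gap for all participants.

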## 4. STUDY POPULATION

### 4.1 Population (base)

Participants will be recruited using different types of media: posters will be hung in the university and hospital, a newspaper advertisement will be placed, social media such as LinkedIn and Facebook will be used, an online advertisement on proefpersonen.nl will be placed. Furthermore, participants from earlier trials who approved to being contacted for future studies will be contacted.

### 4.2 Inclusion criteria

A participant is considered eligible for this study if the following criteria are met:

- Age 30-75 years
- BMI  $\geq 28$  and  $< 40$  kg/m^2
- One or more of the following criteria to determine disturbed glucose/insulin homeostasis:
  - o Fasting glucose 5.6-6.9 mmol/l
  - o HbA1c 42-47 mmol/mol (6.0-6.5%) (36, 37)
  - o HOMA-IR >1.85

### 4.3 Exclusion criteria

A potential subject that meets any of the following criteria will be excluded from participation in this study:

- Diabetes mellitus (type 1 or 2)
- Cardiovascular disease: Including no history of myocardial infarction, heart failure, arrhythmias (except hypertension ( $< 160/100$  mmHg is allowed))
- Pulmonary disease: no history of chronic obstructive pulmonary disease, emphysema, bronchitis, asthma
- Kidney disease/failure
- Hepatic disease/failure
- Gastrointestinal disease or a history of abdominal surgery (except appendectomy and cholecystectomy): No inflammatory bowel disease, irritable bowel syndrome and related diseases.
- Any other diseases affecting glucose and/or lipid metabolism
- Malignancy (except non-invasive skin cancer)
- Auto-immune disease
- Major mental disorders preventing correct participation (such as severe depression, psychosis, schizophrenia)
- Ongoing (infectious) disease or any disease with a life expectancy  $\leq 5$  years

- Substance abuse (nicotine abuse (including e-cigarettes) defined as >20 cigarettes per day; alcohol abuse defined as  $\geq 8$  drinks/week for females and  $\geq 15$  drinks/week for males(38); any drugs)
- A change in weight  $\geq 3$ kg over the last 3 months or plans to lose weight or follow a hypocaloric diet during the study period
- Pre/pro/antibiotic use in the last 3 months or during the study
- Use of medication that influences glucose or fat metabolism and inflammation, such as:
  - o Use of statins (stable use  $\geq 3$  months prior to and during study is allowed)
  - o Use of antidepressants (stable use  $\geq 3$  months prior to and during study is allowed)
  - o Use of anticoagulants (acetylsalicylic acid and carbasalate calcium are allowed)
  - o Use of medication known to interfere with study outcomes
  - o Use of  $\beta$ -blockers
  - o Chronic corticosteroid treatment (>7 consecutive days)
- Regular use of laxatives 3 months prior to the study or during study period
- Change in physical activity or diet during study period
- Intensive physical activity (>3h per week)
- Pregnancy
- Following a vegan or vegetarian diet; presence of food allergies, intolerances or diet restrictions interfering with the study.

#### 4.3.1 Additional exclusion criteria for fMRI

- Metal objects such as implants present in the body (e.g. electronic implants, pacemakers, metal fragments in the eyes, skin or body)
- The use of permanent make-up (eyeliners, eyebrows)
- Tattoos on the head, shoulders, breast or neck
- Claustrophobia

#### 4.4 Sample size calculation

We used G-power to calculate the sample size required to detect a clinically relevant change in peripheral insulin sensitivity.

To calculate the sample size, we used the data derived from previous clinical trials of our research group using a comparable participant population to assess effects of alterations of the gut microbiota on peripheral insulin sensitivity with the hyperinsulinemic-euglycemic clamp technique. Based on the studies' data we calculated a within-group residual SD of 2.70, which was based on a SD of post measurement of 3.95 and a pre-post correlation of 0.73;  $\sqrt{(1-0.732)} \times 3.95 = 2.70$ . Twenty-two (we aim to include an equal number of males and females: 11

males and 11 females) participants per group (N = 44) are needed to detect a physiological relevant difference of 20% (2.86µmol/kg/min) in the change in our primary outcome parameter peripheral insulin sensitivity measured via the hyperinsulinemic-euglycemic clamp technique, assuming a power of 80%, an  $\alpha$ -value of .05, a within-group residual SD of 2.70 and a 20% dropout rate. The described secondary outcomes will be analysed exploratively, for microbiome analysis Benjamini-Hochberg procedure will be used to prevent false-positive results.

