## 10. STATISTICAL ANALYSIS

The statistical analyses will be carried out by the investigator using SPSS software. Regarding descriptive statistics, numerical variables will be reported as mean  $\pm$ SD. Categorical variables will be reported as numbers and percentages. To test for normality of the data, Histogram and Kolmogorov-Smirnov test will be used. In case, of non-parametric data, the data will be transformed using natural logarithm. In general, a p-value  $<0.05$  will be considered statistically significant using two-tailed tests. In case of missing data, we will perform multiple imputation (MI) to estimate the missing value. MI is the process of replacing each missing data point with a set of  $m > 1$  plausible values to generate  $m$  complete data sets. Multiple imputation has been shown to produce valid statistical inference that reflects the uncertainty associated with the estimation of the missing data.

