### 10.1 Primary study parameter(s)

We will be comparing the intervention group versus the placebo group regarding the change in insulin sensitivity as measured by the two-step hyperinsulinemic-euglycemic clamp. Changes in glucose disposal rate and infused glucose concentrations before and after the 12 week intervention period are our primary study parameters and will be analysed and compared between the two groups. Data from both groups will be analysed using a linear mixed model to include repeated measures. An intention-to-treat and per-protocol analysis will be conducted. Intervention and study period will be set as fixed factors, participants will be set as random factor. Age and sex will be added as covariates in the analysis.

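### The stated 22 per group does not follow from its own inputs, which give 20 per group (N = 40) for 80% power; 44 randomised gives about 86%

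*Protocol*

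**What the plan says.** Section 4.4 of the protocol (sample size calculation) used G*Power but does not name the test. It states that 22 "participants per group (N = 44) are needed to detect a physiological relevant difference of 20"%, given as 2.86 µmol/kg/min, in the change in peripheral insulin sensitivity. The calculation is described as "assuming a power of 80"%, with an alpha "value of .05, a within-group residual SD of 2.70 and a 20% dropout rate". The SD is derived in the same section from a post-measurement SD of 3.95 and a pre-post correlation of 0.73: "we calculated a within-group residual SD of 2.70".

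Section 10 says that a p-value below 0.05 "will be considered statistically significant using two-tailed tests". Section 3 has equal randomisation to the two arms.

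For the primary analysis, section 10.1 says: "Data from both groups will be analysed using a linear mixed model to include repeated measures". Intervention and study period are fixed factors, participant is a random factor, and age and sex are covariates. Baseline insulin sensitivity is not among the covariates listed.

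**The concern.** Section 4.4 prints every input needed for a two-group comparison of means, so the sample size can be checked directly, and the check does not return 22. The size and the power quoted beside it therefore do not belong together. Either 44 is more than the inputs need for 80% power, or 44 is the intended number and its power on those inputs is understated by about 6 percentage points.

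This figure is the protocol's justification for the number of people who undergo two clamps and repeated fat and muscle biopsies. A number described as needed should follow from what is printed.

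The kind of SD matters as well. The printed formula gives the SD left after adjusting the post-treatment value for the baseline value. Section 10.1 does not say that the primary model makes that adjustment, so it does not confirm the analysis that the SD assumes.

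**Working it through.** **Inputs.** Difference 2.86, SD 2.70, power 80%, alpha .05 and dropout 20% are from section 4.4. Two-sided testing is from section 10 and 1:1 allocation from section 3.

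**Step 1: the SD reproduces.** √(1 − 0.73²) × 3.95 = 2.6996, or 2.70. The formula in the text at hand shows 0.732, which is 0.73² with the superscript lost. Taken literally, √(1 − 0.732) × 3.95 would be 2.04, not 2.70. The SD is not in error.

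**Step 2: completers needed.** The standardised difference is 2.86 / 2.70 = 1.059. For n completers per arm, the exact two-sample t test has 2n − 2 degrees of freedom and noncentrality 1.059 × √(n/2).

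| Completers per arm | Power |
|---|---|
| 15 | 79.96% |
| 16 | 82.6% |
| 17 | 85.0% |
| 18 and 17 | 86.0% |
| 18 | 87.0% |
| 22 (no dropout) | 92.9% |

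Sixteen per arm is the smallest number that reaches 80%.

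**Step 3: dropout.** 16 / 0.8 = 20 per arm, N = 40. The cruder 16 × 1.2 = 19.2 also rounds up to 20. The protocol has 22 and 44.

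**Step 4: power at the stated size.** 22 × 0.8 = 17.6 completers per arm. That gives 86.2%, and the range from 17 to 18 per arm is 85.0% to 87.0%.

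**Step 5: can another reading return 22 from the stated inputs?**

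- Normal approximation: 2 × ((1.960 + 0.842) × 2.70 / 2.86)² = 13.99, so 14, then 14 / 0.8 = 17.5, so 18.
- One-sided test: 12, then 15.
- Exact t with 1 or 3 degrees of freedom removed for covariates: still 16, then 20.
- Wilcoxon test with efficiency 0.955 inside the power calculation: 16, then 20.
- Equal numbers of men and women: 20 per arm divides evenly too, so this does not force 22.

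Routes that do reach 22 each need something section 4.4 does not state:

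- 85% power by the normal approximation: 17, then 17 / 0.8 = 21.25, so 22.
- The rounded 16 divided by 0.955 for a Wilcoxon test: 16.75, so 17, then 22.
- A Wilcoxon test with the minimum efficiency of 0.864: 18, then 18 × 1.2 = 21.6, so 22.
- A change-score SD of 2.90: 17 by the normal approximation, then 22. By the exact t it gives 18, then 18 / 0.8 = 22.5, so 23.

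**Step 6: if the analysis were an unadjusted comparison of changes.** The change SD is √(SD_pre² + SD_post² − 2 × r × SD_pre × SD_post). The protocol gives SD_post = 3.95 and r = 0.73 but no SD_pre, so SD_pre is an assumption here. Power is for 18 and 17 completers, difference 2.86.

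| Assumed baseline SD | Change SD | Power |
|---|---|---|
| 3.5 | 2.77 | 84% |
| 3.95 (equal to post) | 2.90 | 81% |
| 4.3 | 3.05 | 77% |
| 4.5 | 3.15 | 74% |

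**The case against.** The best case for leaving this alone is that the gap is small and errs on the safe side. It is two people per arm, and 15 completers miss 80% by only 0.04 points. On the printed inputs the trial has more power than it claims, so the primary inference is not threatened. All of that stands and limits the weight of the point. It does not make 22 follow from the inputs.

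A reader might go further and infer that the trial was really sized on a change-score SD of 2.90, that the planned mixed model has about 81% power, and that section 4.4 therefore quotes the SD of the wrong analysis. The document does not support this, for three reasons.

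- The figure of 2.90 needs a baseline SD equal to the post SD, and no baseline SD is given. Plausible values move the power from 84% to 74%.
- Other unstated inputs also return 22, so the source cannot be identified.
- Section 10.1 does not say how baseline enters the model. A pre/post mixed model in which the arms share a baseline mean can be close to a baseline-adjusted analysis in efficiency. One with separate baseline means amounts to a comparison of changes. That detail may stand in a statistical analysis plan that is not at hand.

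A reader might also infer that four people too many are being enrolled. That does not follow either. The inputs need only 40, but nothing shows that 40 rather than 80% is the figure the sponsor would keep, and a margin above 80% is defensible if it is stated.

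Finally, section 8.5 allows withdrawn participants to be replaced, so 17 to 18 completers per arm is not certain. With full replacement the figure would approach 93%.

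**Conclusion.** The point holds as an arithmetic inconsistency. The inputs in section 4.4 give 16 completers and 20 randomised per arm (N = 40) for 80% power, against a stated 22 and 44. At 44, power is about 86% with 20% dropout (85% to 87% for 17 to 18 completers per arm) and about 93% with none.

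This rests on a two-sided two-sample comparison of means at 0.05 with equal arms and the printed SD. It does not change if a few degrees of freedom are taken for covariates. Any further gain in precision from adjusting for age and sex is ignored.

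On these inputs the error is conservative, and its cause cannot be determined from the protocol. Whether power would be above or below 80% under an unadjusted comparison of changes cannot be settled without the baseline SD.

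**What to change.** Keep 44. In section 4.4, name the test and restate the result: with 20% dropout (17 to 18 completers per arm), a baseline-adjusted comparison with residual SD 2.70 has about 86% power, two-sided at .05, for a difference of 2.86 µmol/kg/min. This is the analysis that the printed SD formula assumes. If 22 came from a deliberate margin or another input, state it.

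In section 10.1, add that the primary model adjusts for baseline insulin sensitivity, so that the analysis matches the SD.

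If an unadjusted comparison of pre/post changes is intended instead, replace 2.70 with the change-score SD from the sponsor's own earlier data and give the power that results. The value of 2.90 should not be printed unless those data support it.

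The cost is one paragraph in section 4.4 and one sentence in section 10.1. Enrolment and procedures do not change.
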